## Abstract

**Background:**

Emerging adulthood is often associated with mental health problems. About one in three university students report symptoms of depression and anxiety that can negatively affect their developmental trajectory concerning work, intimate relationships, and health. This can interfere with academic performance, as mood and anxiety disorders are key predictors of dropout from higher education. A treatment gap exists, where a considerable proportion of students do not seek help for mood and anxiety symptoms. Offering internet interventions to students with mental health problems could reduce the treatment gap, increase mental health, and improve academic performance. A meta-analysis on internet interventions for university students showed small effects for depression and none for anxiety. Larger trials are recommended to further explore effects of guidance, transdiagnostic approaches, and individual treatment components.

**Methods:**

This study will offer 1200 university students in Sweden participation in a three-armed randomized controlled trial (RCT) evaluating a guided or unguided transdiagnostic internet intervention for mild to moderate depression and anxiety, where the waitlist control group accesses the intervention at 6-month follow-up. Students reporting suicidal ideation/behaviors will be excluded and referred to treatment within the existing healthcare system. An embedded study within the trial (SWAT) will assess at week 3 of 8 whether participants in the guided and unguided groups are at higher risk of failing to benefit from treatment. Those at risk will be randomized to an adaptive treatment strategy, or to continue the treatment as originally randomized. Primary outcomes are symptoms of depression and anxiety. Follow-ups will occur at post-treatment and at 6-, 12-, and 24-month post-randomization. Between-group outcome analyses will be reported, and qualitative interviews about treatment experiences are planned.

**Discussion:**

This study investigates the effects of a transdiagnostic internet intervention among university students in Sweden, with an adaptive treatment strategy employed during the course of treatment to minimize the risk of treatment failure. The study will contribute knowledge about longitudinal trajectories of mental health and well-being following treatment, taking into account possible gender differences in responsiveness to treatment. With time, effective internet interventions could make treatment for mental health issues more widely accessible to the student group.

## Administrative information

Note: the numbers in parentheses in this protocol refer to SPIRIT checklist item numbers; curly brackets had to be removed due to conflict with the Endnote reference system. The order of the items in has been modified to group similar items according to the journal structured protocol template.

## Introduction

### Background and rationale (6a)

The human developmental trajectory is marked by crucial transitions from one phase to another, for example childhood to adolescence, or late adolescence to emerging adulthood [1]. For many individuals, the latter phase coincides with university studies and is characterized by exploration of identity on a personal and career level [2]. The period is also characterized by a higher rate of engagement in risky behaviors, compared to later adulthood [1]. The variability of life changes and events in emerging adulthood is associated with a high prevalence and incidence of mental health problems. About one in three university students show symptoms of depression and anxiety that can have serious negative effects on the developmental trajectory at work, in intimate relationships and for health [3, 4], and may interfere with academic performance [5]. The most prevalent disorders at this stage include mood, anxiety, and substance use, all key predictors of dropout from higher education [6]. Additional mental problems frequently co-occur with these disorders. Despite the prevalence of mental health problems, students are generally not very likely to seek help, because they either do not believe they need help, experience stigma or lack confidence that they will be helped, or find that they lack quick access to treatment [7]. Cognitive behavioral therapy (CBT) is an internationally widespread treatment method shown to be effective for common mental health disorders, particularly depression [8]. One way to lower the threshold for access to such treatment is to offer internet interventions, which have shown treatment effects for CBT that are equivalent to face-to-face treatment for diagnosis-specific depression, anxiety, and a variety of other conditions [9].

A significant overall research question is whether these internet interventions should be guided by human support. Early studies found that human guidance significantly contributed to reducing attrition as well as increasing treatment effects, and a recent review of 31 meta-analyses confirmed that just under half of reported studies showed that guidance was significantly better than treatment with no human support or minimal such support. At the same time, 9% showed that unguided interventions had better outcomes than supported ones. It is still not clear what factors indicate an obvious need for supported interventions, although the severity of mental health problems might be one indicator [10].

For the target group of university students in particular, a systematic review and meta-analysis of internet interventions to increase students’ mental health showed small between-group effects on measures of depression and no between-group differences on anxiety measures when publication bias was taken into account, where human guidance of interventions did not yield any advantage for the students [11]. In contrast, a later synthesis of data from 18 systematic reviews and meta-analyses for a wider group of adolescents and young people concluded that CBT-based interventions for depression and anxiety could be termed effective, and that involvement of human support could improve effectiveness and intervention adherence [12]. The most recent synthesis of evidence for ICBT interventions for university students, an umbrella review including seven systematic reviews or meta-analyses, found research support for expanding access to digital mental health interventions for university students, and recommended increasing rigor in future studies, including increased analysis of user data on engagement and intervention retention [13]. It thus seems that offering evidence-based guided or unguided internet interventions to students with mental health problems could potentially yield at least some improvements in mental health [3], in the best of cases, participating in such interventions could also contribute to better academic performance and quality of life during the university years, and support improved mental health even past graduation.

To summarize, over the past two decades, diagnosis-specific internet interventions have been thoroughly investigated, with moderate to large effects [9]. The evidence base for internet interventions targeting university students is cautiously positive, but currently not robust [11–13]. The overall research field on digital mental health interventions (DMHIs) has recently been moving towards experimentation with internet interventions that can address more than one condition within the same program; i.e., transdiagnostic interventions based on internet-delivered CBT (iCBT) [e.g., 14]. The advantage of such transdiagnostic interventions is that they can be offered as a “one-size fits all” treatment for individuals with the most common mental health disorders, primarily depression and anxiety. Transdiagnostic interventions for mild to moderate depression and anxiety among university students have been developed and tested in Australia, Canada, Indonesia, the Netherlands, and the UK, [14–20], and results have so far shown minor effects.

Existing research on internet interventions also yields recommendations for larger randomized controlled trials, in order to explore different effects of individual treatment components and the specific role of guidance and/or tailoring of interventions [19]. Further, studies are needed to explore the possibility that internet-delivered CBT (ICBT) for students with symptoms of mild to moderate depression or anxiety might benefit from small improvements that could be clinically relevant [21]. We do not know to what extent internet-delivered transdiagnostic interventions, guided or unguided, could reduce depression and anxiety among university students, nor how long effects might persist, but the existing evidence base suggests that ICBT interventions could have positive effects in the university student group. Additional research is needed to explore if and how transdiagnostic iCBT might yield sustainable post-treatment effects. One factor affecting the lack of positive results in earlier studies could be that treatment protocols need to be designed to deliver greater tailoring in relation to individual needs, as in precision medicine [22]. Students in higher education are clearly in need of effective mental health interventions, and it is a matter of considerable urgency to meet their needs, particularly given that students in Sweden who report mental health problems are twice as likely to drop out without completing a degree [23].

The current study builds on ongoing studies mapping mental health issues among university students in Sweden [24] within the international WHO-WMH-ICS consortium [3]. This study will recruit participants from epidemiological survey respondents at multiple universities, offering participation in a three-armed randomized controlled trial (RCT) that will evaluate guided and unguided internet-based transdiagnostic treatment for depression and anxiety, in comparison to waitlist controls. The transdiagnostic internet-delivered treatment program will also offer user-tailoring of some of the treatment content, an aspect that has shown a small, significant advantage (*d* = 0.26). in comparison to content that is tailored by clinicians [25]. An additional novel feature in this project is that it will encompass a secondary, embedded randomized “study within a trial” (SWAT) [26] that addresses the risk that some of the students in the target group will be less likely to improve in ordinary guided or unguided treatment, and may benefit from an adaptive treatment strategy, which has been shown effective in an earlier trial for insomnia among adults [27]. This embedded trial aligns with a precision medicine approach that adapts treatment content to unique individual needs for increased potential treatment benefits [22].

### Objectives (7)

The overall aim of this trial is to estimate the effects of an internet intervention for common mental health problems among university students in Sweden, who demonstrate mild to moderate symptoms of depression and/or anxiety, who are experiencing lower everyday functionality and whose treatment needs are unmet [6, 28]. Such mild to moderate mental health problems can be both syndromal (i.e., qualify for a psychiatric diagnosis) or sub-syndromal (i.e., be experienced as problematic by the individual, without qualifying for a diagnosis).

The intervention will be transdiagnostic in the sense that participants will select a main focus on depression or anxiety, where the former will entail working with two specific modules on behavioral activation, and the latter will entail working with two specific modules on anxiety exposure. Three modules, the introductory one and the concluding two, will be part of the intervention for all participants. Additionally, the intervention will be tailored in the sense that participants will select three elective modules from a menu of eight, based on their own preferences.

The study design entails offering students in the target group participation in a three-armed RCT evaluating guided or unguided versions of the intervention for a 10-week duration, in comparison to a control group who accesses the unguided version of the intervention 6 months after randomization. The embedded SWAT entails a second randomization procedure 3 weeks into the treatment, where participants identified as being at risk of failing to benefit from treatment will be randomized to receive additional guided support (in the guided arm) or standard guidance (in the unguided arm), or to continue in the guided or unguided treatment arm to which they were originally randomized. Complementary qualitative interviews are conducted to increase understanding of participants’ experiences of the specific treatment received. Students reporting suicidal ideation or behaviors are excluded from the study and referred to treatment within the healthcare system.

Primary outcomes are defined as trial arm comparisons of treatment effects on syndromal and sub-syndromal depression and anxiety. Secondary outcomes are defined as additional exploratory treatment effects related to specific emotional and behavioral changes, well-being, and treatment-related processes such as alliance and negative effects.

The specific objectives are to:Recruit up to 1200 eligible university students.Include students with mild to moderate, syndromal, and sub-syndromal symptoms of depression and/or anxiety symptoms, following brief baseline screening.Randomize included individuals to guided or unguided treatment, or to a waitlist control group accessing treatment 6 months after randomization.Collect weekly data on symptoms of depression, anxiety, and well-being during the 8-week treatment period.In week 3 of 8, to identify participants in the guided and unguided treatment arms, who indicate lack of improvement or worsened symptoms and to randomize them within a SWAT to an adaptive treatment strategy (ATS) or to continue as per their original randomization.Follow up students at post-treatment and at 6-, 12-, and 24-months post-randomization.Undertake qualitative evaluation of students’ experiences of the specific internet treatment received, including those randomized to unguided treatment and those randomized to the ATS.Statistically, we aim to compare primary outcomes between treatment arms, namely treatment effects on syndromal and sub-syndromal depression and anxiety, in relation to the primary hypothesis that both guided and unguided groups will show superior moderate-sized overall effects compared to the waitlist control group, and the secondary hypothesis assumes that the guided group will show no differences in effects in relation to the unguided group.Statistically, we will also compare primary outcomes for individuals in the guided and unguided treatment arms, who participated in the embedded SWAT, in relation to the hypothesis that those who received an ATS will show improved small to moderate effects in comparison to those who did not receive an ATS. A secondary hypothesis regarding the SWAT is that trial retention will be higher for individuals who received an ATS, in comparison to those did not.We will also conduct additional statistical evaluations, comparing secondary outcomes for the main and SWAT trials, with identical hypotheses to those formulated for the primary outcomes.

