### Sample size (14)

We calculated the required sample size based on the smallest effect size on primary outcomes that we did not want to miss, with respect to the contrast between the guided intervention and waiting list control at 6 months post-randomization (T4). We estimated this effect size to 0.3 Cohen’s *d*. With a significance level of 0.05 (alpha) and power of 0.8 (beta), a two-sided *t*-test would require 176 individuals per group, giving a total of 528. Assuming an attrition rate of 40% at T4, this means that we should recruit at least 880 participants. Notwithstanding this power calculation, we hope to extend our recruitment sample to up to 1200 participants if possible, given additional possible attrition after T4 and the importance of reporting outcomes over a longer term than 6 months.

Regarding analysis of the SWAT comparing adapted versus continued standard treatment for at-risk participants, earlier work evaluating for insomnia [33] suggests that between-group differences in final scores corresponding to *d* = 0.4 are possible, which would require *n* = 100 + 100 at-risk participants, i.e., well within the recruitment target.

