## Analysis

### Statistical methods for primary and secondary outcomes (20a)

We will keep participants in the groups to which they were randomized in all analyses (intention-to-treat). We will conduct both available data analyses and analyses with missing data imputed using multiple imputations with chained equations (generating 200 datasets using 30 iterations of predictive mean matching). Both available data and imputed data analyses will be used to interpret findings.

All models of primary and secondary outcomes will be estimated using both Bayesian inference and maximum likelihood estimation [59]. The former will estimate the posterior distribution over effect estimates, while the latter will be used for null hypothesis testing. We will use (half) Student’s *t* priors for covariates, fixed intercepts, and error terms (centered at 0, with a scale of 2.5 and 3 degrees of freedom). Adaptive intercepts in multilevel models will be given standard normal priors. For point estimates, we will report the median of the posterior distribution of each parameter of interest (i.e., group contrasts), along with 95% compatibility intervals defined by the 2.5 and 97.5% percentiles of the posterior distributions. We will use the posterior probability of effect and *P*-values for our scientific inference.

The two co-primary outcomes, anxiety and depression, will be standardized and modeled using a multilevel linear regression model. The models will include a time-by-group interaction with time modeled as a dummy categorical variable (0 = T3, 1 = T4, 2 = T5, 3 = T6), as will group (0 = waiting list, 1 = unguided, 2 = guided). The models will be adjusted for baseline (T1) measures of the outcome variables (respectively) using a baseline-by-time interaction term and further adjusted for age, gender, and a binary variable indicating HBTQ (0 = No, 1 = Yes). Adaptive intercepts will be added to the models at the participant and university level. The linear combination of coefficient estimates for the group and time-by-group covariates will be used as effect estimates (i.e., differences between groups at the different follow-up intervals). For our primary contrasts (guided vs. waiting list and unguided vs. waiting list), we will report effects at T3 and T4. For our exploratory contrast (guided vs. unguided), we will report effects at all four follow-up intervals.

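### The no-difference hypothesis for guided versus unguided treatment has no margin or decision rule, and the inference named in the plan cannot establish similarity

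*Protocol article*

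**What the plan says.** - **Hypothesis.** Objectives (7): "the secondary hypothesis assumes that the guided group will show no differences in effects in relation to the unguided group". The same section extends this to secondary outcomes, "comparing secondary outcomes for the main and SWAT trials, with identical hypotheses to those formulated for the primary outcomes".
- **Inference.** Statistical methods (20a) fits every outcome model twice. Of the Bayesian fit it says "The former will estimate the posterior distribution over effect estimates"; of maximum likelihood, "the latter will be used for null hypothesis testing". Group contrasts are reported as posterior medians, "along with 95% compatibility intervals defined by the 2.5 and 97.5% percentiles of the posterior distributions". The basis for conclusions is then fixed: "We will use the posterior probability of effect and *P*-values for our scientific inference".
- **Status.** Explanation for the choice of comparators (6b) makes the unguided group the secondary comparator for the guided group. Statistical methods (20a) says "For our exploratory contrast (guided vs. unguided), we will report effects at all four follow-up intervals".
- **Sample size.** Sample size (14) covers only guided versus waiting list at 6 months: a superiority test at d = 0.3, two-sided alpha 0.05, power 0.8, giving 176 per group and 528 in total. With 40% attrition this becomes 880 to recruit, with a hoped-for 1200.
- **Margin.** No section gives an equivalence or non-inferiority margin, a region of practical equivalence, or a criterion for concluding that guided and unguided do not differ.

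**The concern.** A hypothesis of no difference needs evidence that the difference is small. Both named tools are built to detect a difference. A P-value against zero is large when the difference is small and also when the data are too few. The article does not define the posterior probability of effect. In its usual sense, the probability that the difference lies on one side of zero, it has the same limitation: a value near one half is compatible with a negligible difference and with an imprecise estimate.

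This is more than detail left to an analysis plan. The article states both a hypothesis and an inferential rule, and the rule cannot evaluate the hypothesis. The background section treats the need for human support as a major open question in the field, so readers will look to this contrast for an answer. The differing labels leave it unclear whether that answer would be a tested hypothesis or a description.

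**Working it through.** **Inputs.** From Sample size (14): d = 0.3, two-sided alpha 0.05, power 0.8, 176 per group, 40% attrition, up to 1200 recruited. Assumptions: SD = 1 (outcomes are standardised), a simple two-sample standard error with no gain from covariates or repeated measures, one outcome at one time point. The equivalence margins are also assumed, because the plan gives none.

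**Step 1: the plan's own figure.** The normal approximation for d = 0.3 gives 175 per group. The t-test solution is 175.4, rounded up to 176. Then 3 × 176 = 528 and 528 / 0.6 = 880. The stated figures reproduce, but for guided versus waiting list.

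**Step 2: precision for guided versus unguided.** SE = √(2/n).
- 176 per arm: SE = √(2/176) = 0.1066; 95% half-width 1.96 × 0.1066 = 0.209 SD.
- 1200 recruited: 1200 × 0.6 / 3 = 240 per arm; SE = √(2/240) = 0.0913; half-width 0.179 SD.

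With 176 per arm, any estimate below 0.209 is non-significant. An estimate just under that value has an upper 95% limit near 0.209 + 0.209 = 0.418 SD.

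**Step 3: chance of a non-significant result when a difference d exists.** P = Φ(1.96 − d/SE) − Φ(−1.96 − d/SE). For d = 0.20 and 176 per arm, d/SE = 1.876, so P = Φ(0.084) − Φ(−3.836) = 0.533.

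| True d | 176 per arm | 240 per arm |
|---|---|---|
| 0.10 | 84% | 81% |
| 0.20 | 53% | 41% |
| 0.30 | 20% | 9% |

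**Step 4: power to show equivalence.** Two one-sided 5% tests (the 90% interval inside ± margin), true difference zero: power = 2Φ(margin/SE − 1.645) − 1. For margin 0.3 and 176 per arm, this is 2Φ(2.814 − 1.645) − 1 = 2Φ(1.169) − 1 = 0.758.

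| Assumed margin (SD) | 176 per arm | 240 per arm | Analysed per arm for 80% power |
|---|---|---|---|
| 0.20 | 18% | 41.5% | 429 |
| 0.25 | 52% | 73% | 275 |
| 0.30 | 76% | 90% | 191 |

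The last column is 2 × ((1.645 + 1.282)/margin)², rounded up.

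**Step 5: effect of baseline adjustment.** The planned models adjust for baseline. If the baseline correlation were 0.5 (an assumption), SE falls by √(1 − 0.25) = 0.866, to 0.0923 with 176 per arm. The 53% becomes about 42%. Equivalence power at a 0.20 margin becomes about 40% (176 per arm) or 62% (240 per arm). The conclusion does not change.

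**The case against.** The strongest reply is that the contrast has low inferential standing. The primary contrasts are each arm against waiting list, only guided versus waiting list was powered, and the analysis section calls guided versus unguided exploratory and promises only to report its effects. A full decision rule for such a contrast could sit in an analysis plan that is not shown. This limits the severity. It does not remove the mismatch, because the objectives still state a hypothesis and the analysis section still states the basis for inference.

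Three stronger readings are tempting, and the protocol supports none of them.

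- *A reader might infer that only a null-hypothesis test is planned.* Statistical methods (20a) also plans posterior distributions and 95% compatibility intervals for the group contrasts. These could be held against a margin; what is missing is the margin and the rule.
- *A reader might infer that a non-significant result will be read as support for no difference, so that losing data helps the hypothesis.* No section says so. The risk follows from the absence of a rule, not from a stated intention.
- *A reader might take the plan's 0.3 as the margin and conclude that the trial can settle the question.* That 0.3 is tied to guided versus waiting list. As a margin between two active arms, it could call them similar even if unguided lost nearly all of the benefit the trial was sized to detect. The background itself reports d = 0.26 as a small but significant advantage in a related comparison, and that would fall inside the margin. The power claim also depends on this choice: at 0.20 SD power is 18% to 41.5%, and even at 0.30 SD the planned 176 per arm gives 76%, below the plan's own 80%.

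**Conclusion.** The point stands in a limited form. The protocol hypothesises no difference between guided and unguided treatment, for primary and secondary outcomes, but gives no margin or decision rule under either analysis, and its named basis for inference cannot establish similarity. The contrast also carries two statuses.

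A non-significant result would be weak evidence: a true difference of 0.20 SD would be missed in about 53% of trials with 176 per arm and 41% with 240. These figures assume SD 1, an unadjusted standard error, one outcome and one time point. Baseline adjustment would lower them but not enough to change the conclusion. Whether the trial could demonstrate similarity depends on a margin that has yet to be justified. The change should be made before the comparison is analysed. It does not touch the primary contrasts.

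**What to change.** Choose one of two routes.

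(a) **Keep the hypothesis.** Prespecify and justify a margin for this active-versus-active contrast, without simply borrowing the 0.3 set for guided versus waiting list. Name one time point. Conclude similarity only if the posterior probability of lying within the margin reaches a prespecified high value, or if the 90% interval lies inside the margin. State the power beside the margin: for 176 to 240 per arm it is about 76% to 90% at 0.30 SD but only 18% to 41.5% at 0.20 SD.

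(b) **Drop the hypothesis.** Report guided versus unguided as exploratory estimation with intervals, and make no claim of similarity from P > 0.05.

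Under either route, give the contrast the same status in Objectives (7), Explanation for the choice of comparators (6b) and Statistical methods (20a), and apply the choice to the secondary outcomes, which inherit the hypothesis.

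The cost is wording plus, for (a), the work of justifying a margin and one further summary of a posterior that is already computed. No new data are needed. The downside is that no difference can no longer be claimed from a non-significant test.
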